### **6.3 Criteria for Withdrawal/ Discontinuation of Participants**

Participants will be withdrawn from the study, if one of the following circumstances occurs:

- The participant withdraws from the informed consent.
- The participant wishes to withdraw from the study.
- The participant experiences unexpected adverse events (severe pain or discomfort) during the intervention implementation

## **7 STUDY INTERVENTION**

### **7.1 General Information**

#### **7.1.1 Study Intervention**

Participants are randomized to an active or control intervention for low back function. Interventionists will alternate for each participant except in cases where the participant specifically requests an interventionist of a preferred gender.

#### ***A) Active intervention***

Mobilization of the low back is performed directly by applying MT to the lumbar paraspinal musculature according to a standardized deep soft tissue procedure. Three paraspinal points on each side are stimulated with circumferential movements initiated by the interventionist's hands (reinforced hand placement), lasting 30 seconds each. The total intervention adds up to three minutes.

#### ***B) Control intervention***

In a standardized deep breathing sequence, patients are instructed to deeply inhale and exhale for 2x3x3 repetitions. Light rhythmic pressure is applied to the thoracic region during expiration with both hands placed on the back, starting at the level of the scapula. The position is adjusted in caudal direction after each repetition. The length of the sham intervention equals the active intervention.

## 7.2 Compliance with Intervention

Definition of non-compliance:

- Inability to follow study instructions provided independent of the eligibility criteria.
- Interruption or premature termination of the intervention due to significant discomfort

## 7.3 Data Collection and Follow-up for Withdrawn Participants

Data collection will be performed according to a predefined sequence of questionnaires as well as measurements of ROM (Table 1). Withdrawn participants will be excluded from further procedures.

**Table 1.** SENSATE trial procedures and timing.

| Outcome                                                                                     | Measure                                                                                                            | Type                 | T -1 | T 0 | T 1 |
|---------------------------------------------------------------------------------------------|--------------------------------------------------------------------------------------------------------------------|----------------------|-----------------|----------------|----------------|
| Demographics                                                                         |                                                                                                                    |                      | x               |                |                |
| Experience with professional MT for the treatment of musculoskeletal disability      | Have you ever received professional manual therapy for the treatment of musculoskeletal disability?                | y/n                  | x               |                |                |
|                                                                                             | Have you ever provided professional manual therapy for the treatment of musculoskeletal disability?                | y/n                  | x               |                |                |
| Exclusion criterion: back surgery                                                    | I have previously had surgery on my back.                                                                          | y/n                  |                 | x              |                |
| Exclusion criterion: serious conditions of the back                                  | I am currently suffering from a serious condition of the back, e.g., fracture, severe scoliosis, cancer.           | y/n                  |                 | x              |                |
| Exclusion criterion: pregnancy or breastfeeding                                      | I am currently pregnant or breastfeeding.                                                                          | y/n                  |                 | x              |                |
| Self-reported back function assessment                                               | How would you rate your back flexibility at the moment?                                                            | 5-point Likert scale |                 | x              | x              |
|                                                                                             | Do you currently experience ache, pain, or discomfort in your upper back?                                          | y/n                  |                 | x              | x              |
|                                                                                             | If yes: How uncomfortable do you feel with the ache, pain, or discomfort in your upper back?                       | 3-point scale        |                 | x              | x              |
|                                                                                             | Do you currently experience ache, pain, or discomfort in your lower back?                                          | y/n                  |                 | x              | x              |
|                                                                                             | If yes: How uncomfortable do you feel with the ache, pain, or discomfort in your lower back?                       | 3-point scale        |                 | x              | x              |
| Thoracolumbar spine flexion–extension                                                | Thoracolumbar angle (Smartphone application)                                                                       | Degrees of motion    |                 | x              | x              |
| Blinding success in outcome assessors                                                | To which extent do you know which intervention (active intervention or control intervention) the patient received? | Blinding index       |                 |                | x              |
| Factors contributing to perceptions about assigned intervention (outcome assessors)  | Please briefly explain your answer regarding the question above.                                                   | Open-ended           |                 |                | x              |
| Blinding success in study participants                                               | To which extent do you know which intervention (active intervention or control intervention) you received?         | Blinding index       |                 |                | x              |
| Factors contributing to perceptions about assigned intervention (study participants) | Please briefly explain your answer regarding the question above.                                                   | Open-ended           |                 |                | x              |

*Note.* MT: manual therapy; y/n: yes–no question; T-1: a day before trial; T0: pre-intervention; T1: post-intervention

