#### **Assessments in Participants who Prematurely Stop the Study**

Participants not complying with interventions or premature exclusion for other reasons are asked to participate in the outcome measurements at least partly (e.g., only questionnaire). If possible, the withdrawal reason is recorded. There will not be any follow-up visits or assessments.

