### Datasets to be Analyzed, Analysis Populations

The analysis population will consist of all participants included in the study as assigned to the respective intervention, following an intention-to-treat approach. Data analysis will be performed by masking (i.e., pseudonymizing) the intervention arm allocation (active or control) of participant data.

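### Sections 7.3 and 8.3 of the Protocol conflict on whether a participant whose session is stopped for discomfort is still asked for outcome data, including the T1 blinding question

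*Protocol*

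**What the plan says.** Five places in the Protocol bear on this.

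- Section 6.3 lists three grounds for withdrawal. Two are the participant's own decision: revoking consent, or wanting to leave. The third is an event in the session: "The participant experiences unexpected adverse events (severe pain or discomfort) during the intervention implementation".
- Section 7.2 counts as non-compliance, among other things, "Interruption or premature termination of the intervention due to significant discomfort".
- Section 7.3 first describes data collection as a set sequence of questionnaires and ROM measurements (Table 1), then states: "Withdrawn participants will be excluded from further procedures". It gives no exception.
- Section 8.3, under the subheading on participants who stop prematurely, states: "Participants not complying with interventions or premature exclusion for other reasons are asked to participate in the outcome measurements at least partly". Its example of partial participation is "e.g., only questionnaire". It also wants the reason for withdrawal recorded where possible, and it rules out follow-up visits.
- Section 10.2 states: "The analysis population will consist of all participants included in the study as assigned to the respective intervention, following an intention-to-treat approach".

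Table 1 places the participants' blinding question at T1 only, and section 8.4 lists it after the intervention.

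**The concern.** Sections 7.3 and 8.3 appear to tell site staff to do opposite things with the same person. Staff who follow 7.3 send the participant away without the blinding question. Staff who follow 8.3 ask for at least some outcome data. The answer at stake is the primary outcome, and with no later visit it cannot be collected afterwards.

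The loss may also not be random. The active procedure is deep soft-tissue work on the lumbar muscles (section 7.1.1 A), and the control is light pressure in time with breathing (section 7.1.1 B). Someone who stops because of discomfort may have formed a view of the arm from that discomfort. If so, the missing answers differ systematically from those collected. Success is judged on whether the point estimate lies between −0.2 and 0.2 (section 10.2), so one or two answers in a small arm can change the conclusion.

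**Working it through.** **1. Who falls under each rule.**

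| Situation | Section 7.3 | Section 8.3 |
|---|---|---|
| Revokes consent, or wants to leave (6.3) | Excluded | No clear conflict: exclusion is ordinary practice |
| Severe pain or discomfort in the session (6.3), which may also be an early stop under 7.2 | Excluded, as withdrawn | Asked for partial data, as a non-complier or early exclusion |
| Non-compliance only (7.2) | Not named | Asked for partial data |

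The clear conflict is in the second row. Section 8.3 speaks of a withdrawal reason, so it cannot be read as covering only people who are not withdrawn.

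**2. When the answer can be obtained.** The question comes after the intervention and there is no follow-up. For someone withdrawn during the session it is therefore a further procedure, and under 7.3 it is never asked.

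**3. The protocol's own precision figure, used to fix the arm size.** Inputs from the Protocol: 26 participants and a half-width of 0.315 (section 10.1), and 1:1 allocation (section 5.1), hence 13 per arm. Thompson's formula is

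n = max over m of z²(1 − α/(2m)) × (1/m)(1 − 1/m) / d².

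With α = 0.05 the maximum is at m = 3, where the numerator is 1.2736.

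- d = 0.315: n = 1.2736/0.315² = 12.84, so 13 per arm.
- n = 13: d = √(1.2736/13) = 0.313, against the stated 0.315.
- d = 0.25: n = 20.4, against the stated 20 or so per group.

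The stated figures reproduce. By the same method, losing one, two or three answers in an arm widens the half-width to 0.326, 0.340 or 0.357. The loss of precision is small.

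**4. Effect on the point estimate.** Take the proportion correct among those who guess in an arm. The formula in section 10.2 then reduces to

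BI = (correct − incorrect) / (correct + incorrect + don't know).

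The counts below are assumed, for one arm of 13.

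| Start (correct / incorrect / don't know) | All asked | 1 correct lost | 2 correct lost | 1 incorrect lost |
|---|---|---|---|---|
| 7 / 4 / 2 | 3/13 = 0.231 | 2/12 = 0.167 | 1/11 = 0.091 | 4/12 = 0.333 |
| 6 / 4 / 3 | 2/13 = 0.154 | 1/12 = 0.083 | 0/11 = 0.000 | 3/12 = 0.250 |

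In the first row, one lost correct guess moves the index by 0.064 and brings it inside ±0.2. The second lost correct guess moves it by a further 0.076. In the second row, one lost incorrect guess takes the index from inside the range to outside it.

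**5. Whether the planned analysis repairs the loss.** Section 10.3 plans multiple imputation (MICE) for missing quantitative data. Suppose the blinding answer is imputed that way. The imputed values then come from participants who completed the session. If stopping depends on the unobserved guess, even after allowing for the variables in the imputation model, the bias remains.

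**The case against.** The case for leaving the text alone has four parts.

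- **The overlap is narrow.** Two of the three withdrawal grounds are a participant's own choice to leave, and excluding those people from further procedures is normal. Section 8.3 only asks, and it offers the questionnaire as an example. This stands, and it confines the point to sessions stopped for discomfort or another reason that is not the participant's wish to leave. It does not remove the conflict for that group.
- **Intention-to-treat is not broken.** A reader might infer that 7.3 contradicts 10.2. It does not: 10.2 says who is analysed and in which arm, and a missing outcome does not void that population. What stands is that the population would contain people whose primary outcome was deliberately not collected.
- **Few people are affected.** Sections 2.4 and 4.3 describe gentle procedures, mild and temporary effects if any, and no anticipated risks. Section 10.3 expects little missing data. This stands, and it limits the practical weight of the point.
- **Bias is inferred.** A reader might conclude that 7.3 biases the active arm towards apparent success, or that the lost answers are the most informative ones. The documents support neither. Nothing says that discomfort reveals the arm or that those who stop would guess correctly, and lost incorrect guesses push the index the other way. The counts in the tables are assumed and sit near the threshold. A shift of 0.064 is also only about a fifth of the half-width (0.064/0.313 = 0.20). It matters because success is read from the point estimate.

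**Conclusion.** The two rules are incompatible for participants whose session is stopped for discomfort or other reasons not amounting to a wish to leave, and nothing in the Protocol says which takes precedence. Following 7.3 would leave their primary outcome uncollected, with no later chance to obtain it. This is a collection rule for the day of the trial, so no analysis plan can make good an answer that was never sought.

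The possible size rests on three assumptions: at least one such stop occurs, the guess is related to stopping, and the arm's index lies near ±0.2. Under those assumptions one or two answers in an arm of 13 can change the conclusion on blinding success, in either direction. The conflict itself is certain. Its effect on the result is possible but not shown.

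**What to change.** Reconcile sections 6.3, 7.3 and 8.3 so that stopping the session and leaving the study are distinct.

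- In 7.3, limit the exclusion from further procedures to participants who withdraw consent or wish to leave the study.
- In 8.3, state that participants whose session is stopped for any other reason are invited, voluntarily, to answer the T1 blinding question and are analysed in their assigned arm. Name the blinding question explicitly, because the present wording gives a questionnaire only as an example.
- In 6.3, align the terms with these two groups. The criteria for stopping the intervention need not change, and none is proposed here.

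The invitation should not reach someone who simply wants to leave, since section 1.5 lets participants withdraw at any time.

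The cost is a few lines of wording and one voluntary question, on the same day, for at most a few people.

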## 8.2 Assessments of Outcomes

### Assessment of Primary Outcome – Blinding success in study participants

The primary outcome of the present study is blinding success in study participants. This will be measured using the Blinding Index according to Bang. The Blinding Index is derived from a five-point Likert scale inquiring about the degree of certainty regarding perceived intervention arm allocation in study participants (1 = “I strongly believe I received the active intervention”; 2 = “I somewhat believe I received the active intervention”; 3 = “I somewhat believe I received the control intervention”; 4 = “I strongly believe I received the control intervention”; and 5 = “I do not know”).

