### Primary Analysis

Blinding indices  $BI_i$  and their respective 95% confidence intervals as defined by Bang et al. will be calculated for each study arm  $i = 1$  for active and  $i = 2$  for sham

$$BI_i = \frac{(2\bar{r}_{i,i} - 1) \cdot (n_{i1} + n_{i2})}{(n_{i1} + n_{i2} + n_{i3})}$$

The Bang index ranges from  $-1$  (opposite guessing related to unblinding) to  $1$  (complete lack of blinding), and can be interpreted as the proportion of participants who guess the intervention correctly over incorrect guesses, including the “don’t know” answer category. In the above formula,  $\bar{r}_{i,i}$  denotes the proportion of correct guesses across the whole population. Successful blinding in the Blinding Index by Bang et al. was predefined as a value from  $-0.2$  to  $0.2$  in the blinding index point estimate. This range will also eventually be used in our analysis as evidence of successful blinding.

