### Secondary Analyses

For our secondary analyses, we will quantitatively evaluate participant’s blinding with James’s BI. The range of this complementary index ranges from  $0$  (all correct) to  $1$  (all incorrect) and does not provide different values according to intervention. An index of  $0.5$  (half correct, half incorrect) indicates random guessing. In addition, we will also assess blinding index in the outcome assessors using Bang’s BI after completing and documenting measurements at  $T_1$ .

Both blinding indices (Bang and James) will be calculated with the R package {BI} based on the participant responses about their degree of confidence in their assigned intervention group (displayed in 5-point Likert scale format).

In the secondary analysis, the measured change in ROM (maximum flexion and extension) of the thoracolumbar spine will be compared within and between the intervention groups (active vs. control;  $T_0$  vs.  $T_1$ ), although formal statistical testing of difference between groups will not be performed, as this would not align with our primary objective. In case a large difference in baseline characteristics is detected between the groups, regression analysis with adjustment of anticipated confounders (i.e., age, gender, experience with MT, care-seeking history for LBP) may be considered.

Contributing factors to perceived intervention arm allocation in study participants, as well as outcome assessors, will be qualitatively analyzed using thematic analysis. Two study investigators will collate collected responses, group them thematically and develop emerging clusters using a consensus-based approach.

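### The blinding items ask what respondents know, but the response options record beliefs and the scoring counts guesses; the wording may raise do-not-know answers and should be aligned

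*Protocol*

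**What the plan says.** Protocol 7.3, Table 1, gives the participant item as "To which extent do you know which intervention (active intervention or control intervention) you received" and the assessor item as "To which extent do you know which intervention (active intervention or control intervention) the patient received". Both are asked at T1, and each is followed by an open-ended request to explain the answer.

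Protocol 8.2 describes the participant scale as "inquiring about the degree of certainty regarding perceived intervention arm allocation in study participants". Two options state a strong belief (active or control), two state a weaker one, such as "I somewhat believe I received the active intervention", and the fifth is do-not-know. The assessor scale has the same structure.

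Protocol 10.2, Primary Analysis, says the Bang index "can be interpreted as the proportion of participants who guess the intervention correctly over incorrect guesses", with do-not-know answers included. Success is a value from -0.2 to 0.2 "in the blinding index point estimate". Under Secondary Analyses, both indices are computed "based on the participant responses about their degree of confidence in their assigned intervention group".

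**The concern.** The question asks about knowledge, the options record belief, and the index treats the answers as guesses. In a trial that conceals the arm, someone who suspects an arm without being sure can truthfully say that they do not know. Under the 8.2 options the same person has a weak-belief category. Which of the two they tick may depend on whether they answer the question or the options, and the text shown contains no instruction to give a best guess.

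This matters because the index handles the two answers differently: a weak belief enters the numerator, a do-not-know answer only the denominator. The same participant answers feed the James index, and the same wording feeds the assessors' Bang index. The item is asked once, at a single visit, so its wording cannot be repaired afterwards.

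**Working it through.** **Inputs from the Protocol.** 26 participants at most (10.1) and 1:1 allocation (5.1), so 13 per arm if all take part. Success range -0.2 to 0.2 on the point estimate (10.2). The share q of hunch-holders who move to do-not-know is not given. Neither are the shares of correct, incorrect, strong and weak answers. All of these are assumed below.

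**The plan's own figure.** 10.1 states a half-width of 0.315. Thompson's worst-case bound takes the maximum over m of z(1 - 0.05/(2m))² × (1/m)(1 - 1/m), which is 1.2736 at m = 3. Then √(1.2736/13) = 0.313, which agrees with 0.315. As a worst-case bound it does not depend on the question wording.

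**The index.** Reading the proportion in the 10.2 formula as correct guesses among those who guessed in that arm, with c correct, i incorrect and d do-not-know answers out of n:

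BI = (2c/(c+i) - 1)(c+i)/n = (c - i)/n.

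The formula has three counts, so strong and weak beliefs count alike. At n = 13 success requires |c - i| ≤ 0.2 × 13 = 2.6, that is, a difference of at most 2.

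**Sensitivity to single answers.**

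| Correct / incorrect / do not know | BI | Within ±0.2? |
|---|---|---|
| 8 / 4 / 1 | 0.308 | no |
| 6 / 3 / 4 | 0.231 | no |
| 5 / 3 / 5 | 0.154 | yes |
| 4 / 2 / 7 | 0.154 | yes |

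From the second row to the third, one correct answer becomes do-not-know and the verdict changes.

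**Diverting hunches only.** Strong answers stay put and a share q of hunches moves:

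BI(q) = (strong correct - strong incorrect) + (1 - q)(hunch correct - hunch incorrect).

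The chance of success is P(|c - i| ≤ 2), by exact trinomial enumeration at n = 13.

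*Case A: 65% correct, 25% incorrect, 10% do not know, half of each guess category being hunches.* At q = 0.25, correct = 0.325 + 0.75 × 0.325 = 0.569 and incorrect = 0.125 + 0.75 × 0.125 = 0.219, so BI = 0.35.

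*Case B: same totals, strong beliefs dominant (strong 40%/10%, hunch 25%/15%).* At q = 0.25, BI = 0.30 + 0.75 × 0.10 = 0.375.

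*Case C: hunches lean against strong beliefs (strong 30%/5%, hunch 20%/30%).* At q = 0.25, BI = 0.25 - 0.75 × 0.10 = 0.175.

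*Case D: balanced (strong 20%/20%, hunch 25%/25%).*

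| Case | BI at q = 0, 0.25, 0.5, 1 | Chance of success at the same q |
|---|---|---|
| A | 0.40, 0.35, 0.30, 0.20 | 18%, 23%, 29%, 47% |
| B | 0.40, 0.375, 0.35, 0.30 | 18%, 20%, 22%, 27% |
| C | 0.15, 0.175, 0.20, 0.25 | 47%, 46%, 45%, 35% |
| D | 0, 0, 0, 0 | 53%, 56%, 61%, 73% |

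In A and B the index moves toward the success range, in C away from it. In D the expected index stays at 0 and only its spread shrinks.

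**The case against.** The strongest reply is that nothing in the Protocol shows anyone being diverted. The question is graded, since it asks to what extent the respondent knows. Respondents presumably answer with all five options in view, and two of those give a hunch an explicit place. A stated belief that matches or misses the true arm is a correct or incorrect guess, so 8.2 and 10.2 agree with each other; what remains is one verb in the question. The open-ended follow-up may also reveal a hunch behind a do-not-know answer, and a 95% confidence interval is reported for each arm.

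Most of this stands as a limit on size and certainty. A reader might infer that participants are in fact steered to do-not-know and that the primary result is therefore biased toward success. The Protocol does not support that: it gives no share of do-not-know answers, and case C shows that the direction is not fixed. Nor do its objectives favour a particular result; they are to assess and compare blinding.

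A reader might also let strong believers move at the same rate as hunch-holders, which gives 18%, 29% and 47% in place of case A's 18%, 23% and 29%. That does not fit the mechanism, which concerns people with only a hunch.

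The reply does not remove the mismatch. The free-text answers do not enter the index, and the success verdict uses the point estimate, not the interval.

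**Conclusion.** The mismatch is real, it is in the current text, and it affects the only item behind the primary outcome as well as the assessors' item. It may raise do-not-know answers. If hunches lean the same way as strong beliefs, that favours a success verdict. In the illustrations, diverting half the hunches raises the chance of that verdict from 18% to 29% (case A) or only from 18% to 22% (case B). These figures rest on assumed answer shares, an assumed q, 13 per arm, and equal weight for strong and weak beliefs as in the 10.2 formula.

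The actual size is unknown and the direction is conditional. This is a cheap improvement to make before the item is used, not a demonstrated bias in the primary outcome.

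**What to change.** In Table 1 and the REDCap forms, word the questions to match the 8.2 options. For participants: *Which intervention do you believe you received, and how strongly do you believe it?* For assessors: *Which intervention do you believe the participant received, and how strongly do you believe it?* Keep the five options and the scoring unchanged. Asking for strength keeps the degree of certainty that 8.2 says the item measures.

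The cost is one sentence in each of two items, with no extra data, staff or time. The downside is possibly fewer do-not-know answers and a slightly wider interval. With half-width 1.96 × √(((c+i)/n - BI²)/n), case A gives 1.96 × √((0.675 - 0.09)/13) = 0.42 with half the hunches diverted and 1.96 × √((0.90 - 0.16)/13) = 0.47 with none. The new wording could also draw guesses from people who have no view, so the do-not-know option must stay.
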